### Outcomes

#### Primary outcomes

Progression-Free Survival (PFS): Defined as the time from randomization to the first occurrence of radiographic disease progression according to RECIST 1.1 (15) criteria or death from any cause, whichever occurs first. Imaging will be performed every 8 weeks from randomization until disease progression, with blinded independent central review.

#### Secondary outcomes

Change in TCM Qi-Yin Deficiency Syndrome Score: The absolute change in the total score from baseline to 6 months (D180 ± 7), assessed using a pre-specified and validated TCM syndrome scale specific for Qi-Yin deficiency in lung cancer. The scale ranges from 0 to 48, with higher scores indicating more severe symptoms. The minimal clinically important difference (MCID) is 4 points. All TCM assessors will undergo a 2-day training session with standardized patients, and inter-rater reliability (kappa ≥ 0.80) will be established prior to study initiation.Objective Response Rate (ORR) and Disease Control Rate (DCR) as per RECIST 1.1 (15).Duration of Response (DOR).Overall Survival (OS).Change in health-related quality of life assessed using the European Organization for Research and Treatment of Cancer Quality of Life Questionnaire Core 30 (EORTC QLQ-C30) (16) and its lung cancer-specific module (QLQ-LC13) (17).Change in Karnofsky Performance Status (KPS) score (18).Incidence, type, severity, and relationship to study treatment of all Adverse Events (AEs) and Serious Adverse Events (SAEs), graded according to the National Cancer Institute Common Terminology Criteria for Adverse Events (NCI CTCAE) Version 5.0 (19).

Evaluation of EGFR-TKIs-related specific adverse reactions:Rash: A validated skin toxicity assessment tool (e.g., HFSR-14 scale or specialized assessment based on CTCAE v5.0 dermatology criteria) will be used to record the incidence, maximum severity (grade), time to onset, duration, and management measures (e.g., topical/systemic medications, dose modifications) of rash.Diarrhea: The incidence, maximum severity (graded per CTCAE v5.0 gastrointestinal criteria), duration, frequency of diarrhea will be recorded, along with the proportion of patients requiring EGFR-TKIs dose modification, interruption, or discontinuation due to diarrhea. The use of anti-diarrheal medications will also be documented.The proportion of patients requiring EGFR-TKIs dose reduction, interruption, or permanent discontinuation due to the above or any other AEs.Changes in serum levels of inflammatory cytokines (IL-2, IL-6, IL-10, TNF-*α*, IFN-*γ*).Changes in peripheral blood lymphocyte subsets (CD3^+^, CD4^+^, CD8^+^, CD4^+^/CD8^+^ ratio, NK cells).Changes in serum tumor marker levels (CEA, CYFRA21-1, SCC-Ag, NSE).

Biomarker sample processing: Blood samples will be collected at baseline, D90, D180, and D365. Samples will be centrifuged within 2 h of collection, aliquoted, and stored at −80 °C. Cytokines will be measured by ELISA, lymphocyte subsets by flow cytometry, and tumor markers by electrochemiluminescence.

Safety will be systematically monitored throughout the study and will include: Physical examinations and monitoring of vital signs at each study visit, with a focus on skin and gastrointestinal symptoms. Regular laboratory assessments: complete blood count, urinalysis, and blood chemistry panels (liver and renal function tests). Electrocardiograms (ECGs) at baseline and as clinically indicated. Ongoing and systematic surveillance, recording, and grading of all AEs according to NCI CTCAE v5.0 (19). Patients will be encouraged to use a standardized diary card to record daily details of skin rash and the frequency/severity of diarrhea episodes to enhance data collection accuracy.

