Several limitations should be considered. As a single-center trial, the findings may have limited generalizability due to local clinical practices and participant characteristics. The complex composition of YFXJD and the limited scope of biomarker analysis constrain mechanistic understanding. Standardizing TCM syndrome differentiation within a clinical trial framework remains challenging. Fourth, the exploratory biomarker analyses are hypothesis-generating and require validation in future studies. Finally, although the use of osimertinib as a uniform background therapy addresses the heterogeneity concern raised by prior studies, the sample size may still be insufficient for robust subgroup analyses.

The CATLA trial (6) previously demonstrated that adding an unspecified Chinese herbal formula to first-generation EGFR-TKIs prolonged PFS. The ongoing CATLA-2 trial (7) is evaluating YYJD combined with osimertinib. Our trial complements these efforts by evaluating a distinct formula (YFXJD) with a different composition and preclinical rationale in a uniform osimertinib background. Positive results would provide evidence for a specific TCM formula that could be integrated into standard osimertinib therapy, while negative results would help refine the selection of herbal formulas for future investigation.

Future multi-center studies with larger sample sizes and more comprehensive mechanistic analyses—including serial ctDNA monitoring and paired tissue analysis at progression—will be necessary to confirm and extend these findings and to establish whether YFXJD specifically affects molecular resistance mechanisms.

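### The single handling rule for biomarker blood (centrifuge, aliquot, freeze at −80 °C) does not exempt the lymphocyte-subset sample and, as written, does not suit flow cytometry

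*Protocol article*

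**What the plan says.** The paragraph on biomarker sample processing in the protocol article (under Secondary outcomes) consists of three sentences.

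- Timing: "Blood samples will be collected at baseline, D90, D180, and D365".
- Handling: "Samples will be centrifuged within 2 h of collection, aliquoted, and stored at −80 °C".
- Assays: "Cytokines will be measured by ELISA, lymphocyte subsets by flow cytometry, and tumor markers by electrochemiluminescence".

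The outcome list just before it names three biomarker families: "Changes in serum levels of inflammatory cytokines", "Changes in peripheral blood lymphocyte subsets" and "Changes in serum tumor marker levels". The lymphocyte family comprises CD3+, CD4+, CD8+, the CD4+/CD8+ ratio and NK cells. Table 2 schedules it at screening (as baseline), D90, D180 and D365. The Objectives section also names lymphocyte subsets among the things the trial will investigate.

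On the status of these measures, the Discussion says that "the exploratory biomarker analyses are hypothesis-generating and require validation in future studies", and the Abstract likewise labels the blood biomarker work exploratory.

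**The concern.** The handling sentence is written without qualification and stands between a sentence about blood draws and a sentence covering three assays. Two of those assays run on serum, for which spinning, aliquoting and freezing is an ordinary route. The third is flow cytometry on lymphocytes, which needs intact cells. The article states a rule and does not exempt the one sample type that the rule does not fit.

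At stake is one of the three biomarker families. If the text were followed to the letter, the lymphocyte results would be missing, or would reflect cell damage from handling rather than treatment. Uneven loss of cell types could shift the CD4+/CD8+ ratio and the NK value. Lymphocyte baselines are drawn at screening, and the Randomization and blinding section places randomization before the first osimertinib dose, so a pre-treatment sample that was mishandled could not be redrawn once treatment had begun.

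**Working it through.** No figure in the plan lies behind this point, so there is nothing to recalculate. The check is a reading of the relevant passages side by side.

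**Step 1: what the handling rule covers.** The timing sentence speaks of blood samples with no division by tube or assay. The handling sentence continues with the same noun, unqualified. The assay sentence then distributes three assays without naming the material for each. On the plain wording, the rule covers the blood for all three.

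**Step 2: what each endpoint needs.**

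| Biomarker family | Material named in Secondary outcomes | Assay | Does spin, aliquot, −80 °C suit it? |
|---|---|---|---|
| Cytokines | Serum | ELISA | Yes |
| Tumor markers | Serum | Electrochemiluminescence | Yes |
| Lymphocyte subsets | Peripheral blood | Flow cytometry | Not as written |

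The last column rests on general laboratory knowledge, not on the article. Serum or plasma aliquots contain no cells to stain, and cells frozen without cryoprotection are largely destroyed. Mononuclear cells that have been isolated and properly cryopreserved can be used, but the article describes no such step.

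**Step 3: whether another place gives the lymphocyte sample its own route.** The Abstract, Table 2, Objectives, Data collection and management, and Discussion all mention biomarkers or biological samples. None mentions fresh anticoagulated blood, mononuclear-cell isolation, cryoprotectant or a time limit to staining. Table 2 gives visits only, and Data collection and management covers recording, storage and retention.

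**Step 4: reach.** The affected measures are the five lymphocyte items at four time points. Nothing in the sample size section, the log-rank or Cox analyses, or the significance level uses them.

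**The case against.** The strongest reply is that this is compressed writing. The outcome list calls cytokines and tumor markers serum measures but describes lymphocyte subsets as peripheral blood measures. A reader who carries that distinction forward could take the freezing sentence as meant for serum only, with subsets run on fresh blood. Tube type, anticoagulant and staining window are details that a journal article commonly leaves to the full protocol or a laboratory manual, neither of which is shown.

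Much of this stands. The missing laboratory detail is not a fault in itself, and the authors may well have intended the serum-only reading. What does not fall away is that the article goes beyond silence: it states a handling rule, and that rule, as worded, takes in a sample it does not suit.

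Two stronger readings are tempting and are not supported.

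- A reader might infer that all biomarker blood is frozen and that flow cytometry is then run on the thawed aliquots, so that the endpoint cannot be measured validly. The article says neither that all blood is frozen nor that thawed material is used, and it is silent on cryoprotectant either way.
- A reader might multiply measures, visits and patients and count every planned lymphocyte result as lost, including the baselines of the 38 patients reported as enrolled under Trial status. Nothing shows that any sample was mishandled. Progression and dropout will also thin the later visits, and the CD4+/CD8+ ratio is derived from two of the other measures.

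**Conclusion.** The point holds as a wrongly scoped handling rule. As written, centrifuging, aliquoting and freezing at −80 °C applies to the biomarker blood without exempting the flow cytometry sample, and literal compliance would give missing or artefactual lymphocyte results at the four sampling times.

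Its size is limited. It touches one exploratory, hypothesis-generating biomarker family and leaves the primary endpoint, the power and the error rate alone. The conclusion rests on two assumptions: that the article's wording reflects the operative instruction, and the general laboratory premise that flow cytometry needs intact cells. If the full protocol or laboratory manual already handles the lymphocyte sample separately, the data are safe and only the published text needs correcting. It is still worth correcting, because a reader of the article cannot tell which is the case.

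**What to change.** 1. Limit the centrifuge and −80 °C sentence to serum for cytokines and tumor markers.
2. State separately that lymphocyte subsets are measured on fresh anticoagulated whole blood within a fixed time window, or on mononuclear cells cryopreserved by a validated procedure. The choice of tube, window and instrument settings can stay in the laboratory manual.
3. For patients already enrolled, document how each lymphocyte sample was handled. Exclude only results from cells frozen without a validated cryopreservation procedure; a blanket exclusion of frozen material would discard usable data.

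The cost is small: a clarified passage in the protocol, possibly one extra small tube at draws already scheduled, and, if fresh blood is chosen, same-day rather than batched flow runs. If current practice already follows such a route, only the text changes.

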### Randomization and blinding

To ensure balanced allocation, centralized randomization using an interactive web response system (IWRS) with variable block sizes (4 and 6) will be performed by an independent statistician. The randomization method will employ a 1:1 allocation ratio using SAS statistical software. Drug packages will be labeled with randomization codes; allocation codes will be sealed and stored separately. Participants will be enrolled sequentially by clinical staff and randomized via the IWRS. The treatment code will be retained by an independent statistician or pharmacy, not the principal investigators. All individuals involved in the trial—including clinicians, nurses, researchers, and patients—will remain unaware of the treatment assignments. Emergency unblinding will occur only when knowledge of assignment is essential for clinical management of a life-threatening condition; an SAE will not automatically trigger unblinding or withdrawal. Participants will be randomized before the first osimertinib dose. In the event of a life-threatening emergency, sealed emergency letters containing unblinding information will be available. A report of any serious AEs must be submitted to the principal investigators within 24 h. After the follow-up period ends, the treatment codes will be disclosed following the completion of data analysis.

### Sample size

The sample size for this study was calculated based on the primary outcome of progression-free survival (PFS). Based on the FLAURA trial, the median PFS for osimertinib monotherapy is approximately 18.9 months. To achieve 80% power at a two-sided significance level of α = 0.05 for detecting a clinically meaningful difference, a target hazard ratio (HR) of 0.66 was assumed, corresponding to a median PFS of approximately 28.6 months in the experimental group (an absolute extension of 9.7 months). This effect size is consistent with the HR observed in the CATLA trial (HR 0.68).

Using the Schoenfeld formula for the log-rank test, the required number of PFS events (d) is calculated as:
$$d=4\times {\left(Z\_(1-\alpha /2)+Z\_(1-\beta )\right)}^{2}/{\left(\ln\;\mathrm{HR}\right)}^{2}$$

With α = 0.05 (two-sided), β = 0.20 (power = 0.80), Z_(1-α/2) = 1.96, Z_(1-β) = 0.84, and HR = 0.66:
$$d=4\times {\left(1.96+0.84\right)}^{2}/{\left(\ln\;0.66\right)}^{2}\approx 176\;\text{events}$$

Under a 1:1 randomization ratio with an accrual period of 12 months, a minimum follow-up of 12 months, and an expected event rate of approximately 65% at the end of follow-up, the required total sample size is approximately 270 patients (135 per group). Accounting for an estimated dropout rate of approximately 20%, we plan to enroll 200 patients (100 per group) to ensure that sufficient patients complete the primary endpoint assessment. The planned enrollment of 200 patients is expected to yield approximately 130 PFS events, providing approximately 75% power at the planned analysis. An interim analysis for futility is planned after 50% of the expected PFS events have been observed, with the option to increase sample size if warranted by conditional power calculations.

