### Additional analyses

Interim analysis for safety and futility is planned after 50% of the planned PFS events have been observed. A futility boundary will be defined using the Lan-DeMets O’Brien-Fleming spending function. The DMC will have clear decision authority regarding continuation, modification, or termination.

Subgroup analyses are prespecified based on factors such as EGFR mutation subtype (e.g., exon 19 del vs. L858R), baseline TCM syndrome score severity, and presence of brain metastases. These analyses are explicitly labeled as exploratory due to limited power for interaction testing.

Logistic regression analysis will be employed to explore factors influencing tumor response rates. A two-sided *p* < 0.05 will be considered statistically significant for the primary endpoint. No adjustment for multiple comparisons will be made for exploratory secondary endpoints, and results for these will be interpreted as hypothesis-generating.

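### Three arithmetic errors in the sample-size section: 182 events are needed, not 176; a dropout allowance cannot lower 270 patients to 200; and 130 events give about 66% power, not 75%

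*Protocol article*

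**What the plan says.** All the figures are in the Sample size section of the protocol article.

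- Target: "To achieve 80% power at a two-sided significance level of α = 0.05".
- Effect: "a target hazard ratio (HR) of 0.66 was assumed", with control and experimental median PFS of 18.9 and 28.6 months.
- Method: "Using the Schoenfeld formula for the log-rank test, the required number of PFS events (d) is calculated as" 4 × (sum of the two z-values)² / (ln HR)². The inputs are "Z_(1-α/2) = 1.96, Z_(1-β) = 0.84, and HR = 0.66", and the printed result is about 176 events.
- Patients: with 12 months of accrual, at least 12 months of follow-up and about 65% of patients having an event, the section arrives at about 270 patients (135 per group).
- Dropout: "Accounting for an estimated dropout rate of approximately 20%, we plan to enroll 200 patients (100 per group").
- Resulting power: "The planned enrollment of 200 patients is expected to yield approximately 130 PFS events, providing approximately 75% power at the planned analysis".

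The Additional analyses section confirms the test: "A two-sided *p* < 0.05 will be considered statistically significant for the primary endpoint". The Sample size section also provides an interim futility analysis at half the expected events, with an option to increase the sample size on the basis of conditional power.

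**The concern.** The section shows its formula and inputs, so each result can be checked, and three do not follow. The event requirement does not match the printed formula. The dropout step moves the sample size the wrong way. The closing power figure is too high for the event count beside it.

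The third matters most, because it tells readers how to interpret a non-significant PFS result. The Discussion says that negative results would help refine the choice of herbal formulas. A negative result from a trial believed to have 75% power is stronger evidence against the assumed effect than one from a trial with 66%. The Trial status section reports 38 patients enrolled by July 2026, so the text can still be corrected well before the analysis.

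**Working it through.** **Inputs**, all from the Sample size section: HR 0.66; two-sided α = 0.05 (z = 1.96); power 80% (z = 0.84); 1:1 allocation; event rate 65%; dropout 20%; planned N = 200. ln 0.66 = −0.4155 and (ln 0.66)² = 0.17265.

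**What reproduces.** 18.9 / 0.66 = 28.6 months. 176 / 0.65 = 271, which matches about 270. 200 × 0.65 = 130 events. These steps are correct on their own inputs.

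**Step 1: required events.** d = 4 × (1.96 + 0.84)² / (ln 0.66)² = 31.36 / 0.17265 = 181.6, so 182. Unrounded z-values give 181.8, so rounding does not explain 176. Freedman's formula gives 188, and a one-sided test gives 144. An HR of about 0.655 would give 176, but the plan does not state that value. At a 65% event rate, 182 / 0.65 = 280 patients; this carries the first error forward and is not a separate one.

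**Step 2: dropout.** The allowance is N / (1 − 0.20): 270 / 0.8 = 337.5, so 338; or 280 / 0.8 = 350. The shortcut N × 1.2 gives 324. Even multiplying by 0.8, which is the wrong direction, gives 216. None of these gives 200.

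**Step 3: power at 130 events.** Power = Φ(|ln HR| × √d / 2 − 1.96).

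| Events d | Power at HR 0.66, two-sided 0.05 |
|---|---|
| 130 | Φ(0.4155 × 11.402 / 2 − 1.96) = Φ(0.409) = 65.9% |
| 161 | 75% |
| 176 | 78.7% |
| 182 | 80.0% |

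Freedman's version gives 64.6% at 130 events. To have 75% power with 130 events, the HR would have to be about 0.63. The HR detectable with 80% power at 130 events is exp(−2 × 2.80 / √130) = exp(−0.491) = 0.61.

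**Where 75% might come from.** A one-sided 5% test at 130 events gives 76.5%, and 160 events two-sided give 74.8%. The plan states neither, so the origin cannot be determined.

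**Sensitivity to the event count (assumptions, not the plan's figures).**

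- If the 65% excludes losses and the 20% who drop out are all lost before any event: 200 × 0.8 × 0.65 = 104 events, and power is Φ(0.159) = 56.3%.
- If PFS is exponential with medians 18.9 and 28.6 months, accrual is uniform over 12 months and minimum follow-up is 12 months, the event probability in an arm with hazard λ is 1 − (e^(−12λ) − e^(−24λ)) / (12λ). This gives 47.9% for control and 35.1% for experimental, a mean of 41.5%. That is 200 × 0.415 = 83 events and about 47% power.

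**The case against.** Several points on the other side stand.

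- A reader might infer that every step is wrong. That is not so: the median conversion, the step from 176 to about 270 and the 130 expected events are all correct on their inputs.
- The 176 against 182 discrepancy is small. With 176 events the power would be 78.7%, about one point below target, and the trial expects 130 events in any case.
- A reader might see a contradiction between 80% and 75%. The documents do not support that. The 80% is the target that leads to about 270 patients, and the plan openly gives a lower figure for 200. The fault is that the lower figure is wrong.
- A reader might take 56% as the power implied by the plan's own dropout rate. That requires that the 65% is not already net of losses and that no dropout has an event first, and the plan says neither. Patients who stop the intervention are encouraged to stay in follow-up (Withdrawal/termination criteria), the analysis includes all randomised patients (Statistical analysis), and patients without progression are censored at last known follow-up (Handling of missing data), so they can contribute events before loss.
- The 200 may not be final, because the plan keeps an option to increase it.
- The errors leave type I error and the analysis method untouched.

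None of this rescues the 75%. The option to increase the sample size is conditional and does not make the power stated for 200 patients true. A one-sided test would come close to 75%, but both relevant sections specify a two-sided test. The point concerns printed figures that disagree with each other, so it does not depend on what a fuller protocol or analysis plan might contain.

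**Conclusion.** The point holds, limited to three errors. The required events are 182, not 176. The dropout allowance runs in the wrong direction and cannot justify 200 patients. Power at the expected 130 events is about 66%, not 75%, an overstatement of about 9 percentage points. Against the 80% target the shortfall is about 14 points; the plan discloses 5.

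The 66% rests on HR 0.66, the two-sided 5% log-rank test, proportional hazards and 130 events being observed. It accepts the plan's 65% event rate. The 56% and 47% figures are scenarios under added assumptions; they show that 66% may be optimistic, but they are not the plan's own results. A reader might also suppose that 200 was chosen for feasibility. The document does not say so, and only the sponsor can give the reason.

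**What to change.** Amend the Sample size section, leaving enrolment as planned:

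1. State that 182 PFS events are required for 80% power at HR 0.66, two-sided α = 0.05, which corresponds to about 280 patients at a 65% event rate and 350 with a 20% dropout allowance.
2. Delete the statement that 200 patients accounts for 20% dropout, and have the sponsor give its actual reason for 200.
3. Replace 75% with about 66%, conditional on 130 events, and add that the HR detectable with 80% power at 130 events is about 0.61.
4. Report lower-event scenarios, labelled as assumptions: about 56% power at 104 events if 20% of patients are lost before any event, and about 47% at about 83 events if PFS is exponential with the stated medians, 12-month accrual and 12-month minimum follow-up. Say whether the 65% event rate is net of losses.

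The cost is a wording amendment, which under the Ethics and dissemination section needs ethics committee approval, and a less favourable stated power. No additional patients are needed for the correction itself.
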